### **3. RESEARCH DESIGN/METHODS/ANALYSIS**

#### **3.1. Study Design**

This study is a Phase I pre-pilot open-label trial of nabilone in adults with IDD and SBP. As shown in Figure 1, the trial first includes a screening visit (S-V) for eligibility, then a baseline visit (V 0), followed by a dose titration phase, and then a 4-week open label phase at a stable dose. At the end of the open label phase, participants will undergo a termination visit (V 1), after which nabilone will be tapered off over 8 days. And then, 2 weeks later, participants will undergo a last follow-up visit (V-F) to ensure safety.

At S-V, and before the informed consent process, the participant will be assessed for capacity to provide informed consent. If they cannot pass the competence test using the MacArthur Competence Assessment Tool for Clinical Research (MacCAT-CR), then the written informed consent will be obtained from their substitute decision maker after seeking participants' assent.

At S-V, participants will also be assessed for eligibility based on the inclusion and exclusion criteria, including SBP defined as a score  $\geq 18$  on the Aberrant Behaviour Checklist-Irritability

subscale (ABC-I) and a score  $\geq 4$  on the Clinical Global Impressions-Severity scale (41). The SBP should present with a consistent pattern with the frequency of  $\geq 1$  time per week for  $>3$  months.

If it is deemed necessary, research staff may review participants' medical charts to obtain clinically relevant information and/or additional information to confirm their eligibility. The investigator or research staff may also request information from the participant's physician.

At V 0 the following assessments will be completed:

- Clinical Global Impression – Severity scale (CGI-S) will be rated by the investigator to evaluate the severity of the behavioural problems.
- Measuring baseline vital signs and weight to monitor any AEs of nabilone.

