- Assessment of adverse events using the UKU side effect rating scale, examined by the researcher or investigator, to systemically investigate the physical AEs of nabilone.
- Re-measuring of vital signs (including blood pressure to check orthostatic hypotension) and weight to monitor the physical AEs of nabilone.
- Re-assessment of participants' cognitive capacity using the NIH Toolbox® Cognition Battery, to monitor any acute cognitive change (AEs) due to nabilone.
- Re-assessment of caregiver rated ABC-I, MOAS, and General Anxiety Subscale of ADAMS. CGI-S and CGI-I will be rated by the investigator to evaluate the severity and improvement of the behavioural problems after nabilone treatment. These re-assessments are implemented to fulfil the exploratory study aim of assessing behavioural changes pre- and post-treatment of nabilone.
- Re-assessment of caregiver's stress and crisis using the Stress Subscale of DASS-21 and BFDS, to investigate changes in their stress and distress after participants takes nabilone.
- Optional re-assessment of MRI Imaging for those who finish the pre-treatment MRI and are willing to receive the second wave of MRI imaging. This is to investigate the change in brain function and structure pre- and post-treatment of nabilone.

Nabilone will be tapered in 0.25 mg daily decrements to prevent acute withdrawal effects. This This proposed down-titration schedule was decided based on a conservative modification from a clinical trial of using Nabilone to treat behavioural and psychological symptoms of dementia (27). Phone calls will be held every other day during the dose-tapering phase, to check whether there are any changes which are believed to be attributed to withdrawal effects. A safety follow-up visit (S-F) will be scheduled after 2 weeks of full discontinuation from the study drug.

The study team will pick up the blister pack from Research Pharmacy, and then distribute to the participant/caregiver. Upon receipt of the nabilone supplies, an inventory will be performed and a receipt log filled out and signed by the research staff who picks up the blister pack. Designated research staff/pharmacy must count and verify that the pickup contains all the items noted in the

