### 3.2. Assessments and visits (Table 1):

Screening assessments for participants and their caregivers include:

- Assessment of prior medical records to collect information of previous cognitive assessment regarding IQ, status of Disability of Ontario Services (DSO), co-occurring physical and psychiatric diagnoses, medication use and potential changes.
- Assessment of capacity to make an informed consent based on both the MacArthur Competence Assessment Tool for Clinical Research (MacCAT-CR) (44) and clinical assessment (45). This will be carried out before the informed consent process and formal assessment.
- Interview of the Moss Psychiatric Assessment Schedules (Moss-PAS (ID)) to the caregiver to assess for co-occurring mental health conditions.
- The Adaptive Behavior Assessment System, Third Edition (ABAS-3), Adult Form, will measure adaptive behaviour and function.
- Measuring of vital signs, weight and height.
- Urine pregnancy test for sexually active women of child-bearing potential.
- Caregiver rated Aberrant Behavior Checklist-Irritability subscale (ABC-I) will be used to define the SBP. Clinical Global Impression – Severity scale (CGI-S) will be rated by the investigator to evaluate the severity of the behavioural problems.

Baseline (pre-treatment) assessments include:

- Measuring of vital signs and weight.
- Assessment of participants' cognitive capacity using the NIH Toolbox® Cognition Battery.
- Assessment of SBP of participants using the ABC-I and MOAS, and anxiety using the General Anxiety Subscale of the ADAMS, as reported by the caregivers.
- Assessment of caregiver's stress and crisis using the Stress Subscale of DASS-21 and BFDS.
- Exploratory assessment of autism symptoms using the Social Communication Questionnaire for Adults with Intellectual Disability (SCQ-AID).

- Optional assessment of MRI Imaging (dependent on the participant's ability to comply with the following assessments, in the opinion of the carers/parents and investigator).
- Concomitant medication

Post-treatment assessments include:

- Assessment of adverse events using the UKU side effect rating scale, examined by the researcher or investigator.
- Re-measuring of vital signs and weight.
- Re-assessment of participants' cognitive capacity using the NIH Toolbox® Cognition Battery.

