#### Scales to measure overall clinical impression

Clinical Global Impressions (CGI) scale: The CGI is a well-established research rating tool to provide a brief, stand-alone assessment of the clinician's view of the patient's global functioning prior to and after initiating a study medication (54). The CGI-Severity (CGI-S) asks the clinician one question: "Considering your total clinical experience with this particular population, how mentally ill is the patient at this time?" which is rated on the following seven-point scale: 1=normal, not at all ill; 2=borderline mentally ill; 3=mildly ill; 4=moderately ill; 5=markedly ill; 6=severely ill; 7=among the most extremely ill patients. This rating is based upon the average severity of observed and reported symptoms, behaviour, and function in the past seven days. The CGI-Improvement (CGI-I) is for the clinician to compare the patient's overall clinical condition to the baseline visit and is rated on a seven-point scale: "Compared to the patient's condition at admission to the project [prior to medication initiation], this patient's condition is: 1=very much improved since the initiation of treatment; 2=much improved; 3=minimally improved; 4=no change from baseline (the initiation of treatment); 5=minimally worse; 6= much worse; 7=very much worse since the initiation of treatment." <5 minutes to complete.

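### Sections 3.1 and 3.2 and Table 1 disagree on the CGI schedule: CGI-S may be missing at V 0, leaving a score selected at 4 or above as its only pre-treatment value, and Table 1 marks CGI-I where it has no meaning

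*Protocol*

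**What the plan says.** Three places in the protocol set the CGI schedule.

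- **Section 3.1.** The first item in the V 0 list states that "CGI-S) will be rated by the investigator to evaluate the severity of the behavioural problems". For V 1 it states that "CGI-S and CGI-I will be rated by the investigator to evaluate the severity and improvement of the behavioural problems after nabilone treatment". It places no CGI-I at V 0.
- **Section 3.2.** CGI-S is in the screening list. The list that opens "Baseline (pre-treatment) assessments include" contains "Assessment of SBP of participants using the ABC-I and MOAS, and anxiety using the General Anxiety Subscale of the ADAMS", but neither CGI-S nor CGI-I. Both scales are in the post-treatment list.
- **Table 1.** CGI-S is marked at S-V and V 1, with V 0 empty. CGI-I is marked at V 0 and V 1.

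Section 3.4 says the CGI-I "is for the clinician to compare the patient's overall clinical condition to the baseline visit". It says the CGI-S reflects symptoms, "behaviour, and function in the past seven days". Sections 3.1 and 3.3 require a CGI-S of at least 4 for entry, assessed at screening. Section 8 plans paired t-tests of pre- versus post-treatment behavioural change in one arm, with 30 participants expected.

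**The concern.** Two things go wrong if site staff work from Table 1.

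First, a CGI-I at V 0 has nothing to refer to. V 0 is the baseline visit and nabilone starts after it, so a rating of change since baseline is empty at that visit.

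Second, the only CGI-S before treatment is then the screening score, and that score decided who entered. People whose rating happened to be high on the screening day are over-represented among those who pass the cut-off, so a repeat rating is lower on average even with no treatment effect. There is no control arm in which to see this drift. Following the Section 3.2 list has the same result for CGI-S.

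The protocol avoids this arrangement for its other selection score: ABC-I is taken at screening and again at V 0, in both text and table. A V 0 rating that was never taken cannot be recovered at analysis. If staff follow different sections, some participants will have a V 0 CGI-S and others will not.

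**Working it through.** **1. The schedules side by side**

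| Source | CGI-S at S-V | CGI-S at V 0 | CGI-S at V 1 | CGI-I at V 0 | CGI-I at V 1 |
|---|---|---|---|---|---|
| Section 3.1 | yes (eligibility) | yes | yes | no | yes |
| Section 3.2 | yes | no | yes | no | yes |
| Table 1 | yes | no | yes | yes | yes |

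Section 3.1 stands alone on CGI-S at V 0. Table 1 stands alone on CGI-I at V 0.

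**2. The plan's own figure**

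Section 8: 40 x 0.75 = 30 participants. For a paired t-test with n=30 (29 df, noncentral t) and two-sided alpha 0.05, power at d = 0.53 is 0.801, and the smallest d with 80% power is 0.529. The stated 0.53 reproduces and is not affected by this point.

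**3. Size of the drift if screening is the baseline**

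The cut-off of 4, the 1 to 7 scale and n=30 are from the protocol. The rating SD of 1, the candidate mean before selection (3.5 to 5.0), the retest correlation r (0.7 to 0.9, equal between all visits) and the absence of a drug effect are assumptions.

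The expected change from S-V to V 1 is -(1 - r*) x (mean of selected scores - mean of all scores). Here r* is the correlation of the rounded scores, about r / (1 + 1/12).

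Example with mean 4.0 and r = 0.8:
- r* = 0.8 / 1.083 = 0.738.
- The rounded scores 4, 5, 6 and 7 have probabilities 0.383, 0.242, 0.061 and 0.006, so the mean given a score of at least 4 is 4.55.
- The change is -(1 - 0.738) x 0.55 = -0.14.

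Simulation on the rounded scale (4,000,000 draws per cell) gives the table below. The standardised change dz is the mean change divided by its SD, and rejection comes from the noncentral t with noncentrality dz x sqrt(30).

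| Candidate mean | r | Change, S-V to V 1 | dz | Rejection at n=30 |
|---|---|---|---|---|
| 3.5 | 0.7 | -0.31 | -0.37 | 51% |
| 4.0 | 0.8 | -0.15 | -0.20 | 19% |
| 4.5 | 0.8 | -0.08 | -0.11 | 9% |
| 4.5 | 0.9 | -0.05 | -0.09 | 8% |
| 5.0 | 0.8 | -0.04 | -0.05 | 6% |
| 5.0 | 0.9 | -0.03 | -0.04 | 6% |

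A second set of assumptions (mean 4.0 to 5.0, SD 0.8 to 1.2, reliability 0.5 to 0.9) gives -0.01 to -0.37 points and 5% to 39% rejection. Its middle case (mean 4.5, SD 1.0, reliability 0.65) gives -0.13 points and 11.5%.

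**4. The same with V 0 as baseline**

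- Equal correlations between visits and no selection at V 0: expected change 0.00 in every case.
- Unequal correlations (assumed S-V to V 0 0.9, V 0 to V 1 0.8, S-V to V 1 0.72; means 3.5 to 4.5): -0.05 to -0.15 from V 0, against -0.10 to -0.29 from S-V. The drift is halved.
- Equal correlations, but participants with a V 0 score below 4 also removed: -0.02 to -0.21 over means 3.5 to 5.0.

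**The case against.** The bias is conditional. Section 3.1 does schedule a V 0 CGI-S, and nothing in the protocol names the screening score as the pre-treatment value. The marks in two adjacent rows of Table 1 look like a row slip. A reader might infer that the screening score is the CGI-S baseline by design; the documents support only that it becomes so if Table 1 or Section 3.2 is followed. A reader might also infer that Table 1 contradicts the text as a whole, but Section 3.2 is text and agrees with it in leaving CGI-S out of V 0.

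A reader might further take the V 0 mark on CGI-I to imply a paired test of CGI-I from V 0 to V 1. Section 8 names no CGI-I analysis, so that is not supported, and how CGI-I is analysed can be left to the analysis plan.

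The stakes are modest. The primary objective is safety and tolerability, Section 3.1 makes ABC-I and MOAS the principal measures of behavioural change, and CGI-S is a secondary row. The 51% also needs a candidate mean below the cut-off, at which half of candidates would fail on CGI-S alone. Candidates must also score at least 18 on ABC-I and show weekly behaviour problems for more than three months, so a higher mean is plausible.

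All of this limits the weight of the point. It does not settle which schedule staff will follow, and it gives a V 0 CGI-I no meaning.

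**Conclusion.** The contradiction is established from the document alone: three places give the CGI schedule and no two agree in full. The CGI-I mark at V 0 is wrong by the protocol's own definition of the scale.

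The bias in CGI-S change is a possible consequence whose direction, toward improvement, is clear. Its size cannot be fixed from the documents, and the upper figures should not be read as expected values. It is negligible if most candidates score well above 4 and appreciable if the candidate mean is near or below 4.

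It would also be too strong to say that a V 0 baseline removes the bias. That holds only if correlations between visits are equal and nobody is re-selected on the V 0 score. Section 7.1 lists ceasing to meet inclusion criteria as a reason for withdrawal, so re-selection cannot be ruled out.

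The safety and tolerability aims, the ABC-I comparison and the sample-size figure are untouched. The point still deserves correction because the results are meant to inform the follow-up trials.

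**What to change.** - In Table 1, mark CGI-S at S-V, V 0 and V 1, and CGI-I at V 1 only.
- Add CGI-S to the baseline list in Section 3.2, so that it agrees with Section 3.1.
- State that the V 0 rating is the baseline for CGI-S change.

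The cost is two table cells and two lines of text, plus one investigator rating that Section 3.4 puts at under five minutes and Section 3.1 already schedules.

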After V 0, eligible participants will receive open-label nabilone starting with a dosage of 0.25 mg before sleep. During the dose titration phase (which could last up to 15 days), nabilone will be titrated in 0.25 mg increments every two days (with the dosing schedule "twice daily") after consultation with the study team during regular phone calls. This proposed up-titration schedule was decided based on a clinical trial of using Nabilone to treat non-motor symptoms in adults with Parkinson's disease (30). These regular phone calls will be carried out every two days during the whole dose titration phase until the participant reaches a stable dose for the open-label phase. The study team will also check whether the participants show any physical or mental changes which are believed to be attributed to AEs (based on the UKU side effect rating scale), and advise the participant and their caregivers on the next step of titration accordingly. Dose adjustments are

performed until the participant reaches the maximum permitted dose of 1 mg twice daily or experience intolerable AEs believed to be related to nabilone. If intolerable, the participant will use nabilone at the previous lower dose, entering the open label phase. Note that the suggested maximum nabilone daily dose per the product monograph is 6 mg. However, considering the vulnerability of the current target population, we choose to administer 2 mg/day at most in the current proposal following the maximum dose used in clinical trials in people with dementia (27) and Parkinson's disease (30). Moreover, nabilone is a THC analog; THC appears to reduce anxiety at low doses but becomes anxiogenic at high doses. Thus, administering nabilone at lower doses is theoretically consistent with the treatment objective for SBP.

Participants will be then on a stable, optimized nabilone dosage for four weeks, and then the trial ends with an on-site termination visit (V1). During the open-label trial phase, the study team will call the participant and their caregivers once weekly to perform a basic check-up, and to follow up with any questions or concerns from the trial processes. If there are any changes suspected to be associated with AEs, the UKU side effect rating scale will be assessed during the telephone check-up.

At V 1, the following post-treatment assessments will be completed:

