shipment inventory. Any damaged or unusable nabilone in a given pick-up will be documented in the clinical trial files. Regarding dispensing the study medication, participants/caregivers will come to CAMH at 3 separate times to pick up nabilone (Table 1), including 1) to pick up the package for the whole dose titration phase and the first 6 days of the stable dose phase at the Pre-treatment Visit (V 0), 2) to pick up the package for the remaining days of the stable phase, and 3) to pick up the package for the dose tapering phase at the Post-treatment Visit (V 1). Nabilone will be prepared for each visit by Research Pharmacy Service. Participants/caregivers will be requested to document the details of using nabilone and other concomitant medications in the drug diary. They will also be asked and expected to return the empty or any leftover nabilone back to the study team, to help with drug accountability.

Regular study intervention reconciliation will be performed to document nabilone assigned, consumed, and remaining. This reconciliation will be logged on a drug accountability log, and signed and dated by delegated research and/or pharmacy staff.

At the completion of the clinical trial, there will be a final reconciliation of the nabilone dispensed, consumed and remaining, based on the drug diary, the remaining drugs which are returned. This reconciliation will be logged on an accountability form, and signed and dated by delegated research and/or pharmacy staff. Any discrepancies noted will be investigated, resolved, and documented prior to return or destruction of unused study intervention. Intervention destroyed on site will be documented in the clinical trial's files.

All participants entering the dose titration phase will be included in the description of the safety profile and tolerability of nabilone (the Primary Objective). Participants completing the dose titration stage will be included in the final statistical analysis for the Exploratory Objective (i.e., explore changes in SBP in participants pre-and post-treatment), regardless of whether they complete the full protocol. This approach is consistent with the intention-to-treat principle.

**Figure 1.** A schematic diagram of the study procedures, including all study visits and timelines. Abbreviation: S-V: a screening visit; V 0: a baseline visit; V 1: a visit at the end of open label phase; V-F: a follow-up visit to ensure safety; d: days; wk: weeks; FU: follow-up; max: maximum.

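### The titration timetable reaches 2.0 mg/day on its last permitted day, so the top dose has no scheduled two-day adverse-event check before it is treated as stable

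*Protocol*

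**What the plan says.** All of the dosing rules are in Protocol Section 3.1. Nabilone starts at 0.25 mg at bedtime, and then: "During the dose titration phase (which could last up to 15 days), nabilone will be titrated in 0.25 mg increments every two days". Each increase follows a call with the study team, at which side effects are reviewed against the UKU scale.

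Dose changes are to be "performed until the participant reaches the maximum permitted dose of 1 mg twice daily or experience intolerable AEs believed to be related to nabilone". The next sentence reads: "If intolerable, the participant will use nabilone at the previous lower dose, entering the open label phase".

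On contact, the section says: "These regular phone calls will be carried out every two days during the whole dose titration phase until the participant reaches a stable dose". In the four-week stable-dose phase that follows, "the study team will call the participant and their caregivers once weekly to perform a basic check-up".

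Two other statements in Section 3.1 help to fix the size of a step and the supply. After the termination visit comes a taper, "after which nabilone will be tapered off over 8 days", and "Nabilone will be tapered in 0.25 mg daily decrements to prevent acute withdrawal effects". The first of three dispensing occasions, at the baseline visit, is "to pick up the package for the whole dose titration phase and the first 6 days of the stable dose phase".

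Section 12 has adverse events assessed at every visit and call. It also returns the open-label calls to every two days for a participant who continues with tolerable adverse events.

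**The concern.** At each lower dose the participant takes the dose for two days, a call follows, and only then is the next step decided. The highest dose ought to get at least the same check, because this is a Phase I trial whose primary objective is tolerability and safety. Section 1.2 of the Protocol says that people with IDD have a higher risk of psychotropic side effects and are less able to report them, so a scheduled contact is worth more here than reliance on spontaneous reports. Section 3.1 itself gives the vulnerability of this population as the reason for capping the dose at 2 mg/day.

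If the timetable ends as soon as 2.0 mg/day is reached, the one dose that no later titration step follows is also the one that can be called stable without a planned look at how it is tolerated. What is at stake is a few days' delay in finding early intolerance of the top dose.

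**Working it through.** **Inputs (Protocol Section 3.1).** Start 0.25 mg/day; step 0.25 mg; interval 2 days; maximum 1 mg twice daily = 2.0 mg/day; titration up to 15 days; taper 8 days in 0.25 mg daily decrements; first package = titration plus 6 stable days.

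**Reproducing the 15-day limit.** Take each step as 0.25 mg of total daily dose and the first dose as day 1.

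- Steps needed = (2.0 − 0.25) / 0.25 = 7.
- First day at 2.0 mg/day = 1 + 7 × 2 = day 15.

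| Day of first intake | 1 | 3 | 5 | 7 | 9 | 11 | 13 | 15 |
|---|---|---|---|---|---|---|---|---|
| mg/day | 0.25 | 0.50 | 0.75 | 1.00 | 1.25 | 1.50 | 1.75 | 2.00 |

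This gives exactly the stated 15 days. The taper agrees with it: 2.0 / 0.25 = 8 daily decrements.

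**Where the check of each dose falls.** A dose begun on day *d* is checked on day *d* + 2, after two days of intake. For 1.75 mg/day that is 13 + 2 = day 15, inside titration. For 2.0 mg/day it is 15 + 2 = day 17, after titration has ended. Two days at each of 8 levels takes 8 × 2 = 16 days, against 15 allowed.

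**Day-count variant.** If the first bedtime dose is day 0, 2.0 mg/day starts on day 14 and is taken on days 14 and 15. Its check falls on day 16, still after the limit.

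**Step-size variant.** If 0.25 mg were added to each of two daily doses, the sequence would be 0.25, 0.5, 1.0, 1.5 and 2.0 mg/day on days 1, 3, 5, 7 and 9. The maximum would come on day 9, with ample time for a check. But this does not explain a 15-day limit, and it fits the 0.25 mg daily taper less well. It is possible, but not the natural reading.

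**Next scheduled contact after the last increment (day 15).**

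- Second drug pick-up: the first package covers 15 + 6 = 21 days, so pick-up is due by day 21, and 21 − 15 = 6 days.
- First weekly call: with the open-label phase starting on day 15, day 22, and 22 − 15 = 7 days; starting on day 16, day 23, and 8 days.

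The first of these contacts therefore comes about 6 to 7 days after the increment, compared with 2 days at every lower dose. A call on day 17 would bring it forward by up to 21 − 17 = 4 days relative to the pick-up.

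**The case against.** The strongest reply is that nothing is missing. The step-back sentence comes directly after the sentence that names the maximum dose, excludes no dose and sets no day limit. A reader might infer from the timetable that a participant who cannot tolerate 2.0 mg/day has no route to 1.75 mg/day. The text does not support that inference, and this part of the reply stands.

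The two-day calls are also said to run until a stable dose is reached, which is not the same as the first intake of 2.0 mg/day. Staff could reasonably keep calling until that dose has proved tolerable. This stands as a possible reading, but it overruns the stated 15 days, and Section 3.1 makes reaching the maximum an end point of adjustment in its own right. The text does not schedule the call.

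Nor are participants at the top dose unmonitored. There are weekly calls, the pick-up, caregiver reports and, under Section 12, two-day calls for those continuing with tolerable adverse events. The cap is also one third of the 6 mg/day monograph maximum. All of this limits the weight of the point. The extra calls in Section 12, however, depend on an adverse event already being known, so they do not replace a first planned check.

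A reader might also infer that the completion rate of Hypothesis 1 is distorted, because intolerance could be handled as a step back or as a withdrawal. One participant among 40 is 1/40 = 2.5 percentage points, but the documents do not say how many would first become intolerant just after reaching 2.0 mg/day, and the number may be zero. No effect on that rate is shown.

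Finally, Figure 1, which carries the timelines, is not available here and may add detail.

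**Conclusion.** The point holds as a minor timing gap. On the natural reading, 2.0 mg/day begins on the last permitted titration day, and its two-day check falls on day 17 (day 16 if counting starts at 0), after the phase has ended. It is the only dose without that check in the schedule. The next planned contact may be about 6 to 7 days after the last increment instead of 2.

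This rests on three assumptions: steps are in total daily dose, a participant moves up at every two-day call, and no adverse event is reported in between. It does not depend on whether the first dose is counted as day 0 or day 1. It would fall away if the increments were meant per dose.

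The defect is when the check takes place. It is not the absence of a step-back rule or a demonstrated bias in the primary result.

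**What to change.** In Section 3.1 of the Protocol:

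- Let titration last up to 16 days, so that all eight levels can be taken for two days.
- Keep the two-day calls through the call two days after the last increment (day 17 for those who reach 2.0 mg/day), and require that call before the dose is declared stable. Day 17 matches the lower doses, each of which is also checked on the day after its second day of intake.
- Confirm in one sentence that intolerance of 2.0 mg/day leads to 1.75 mg/day and entry to the open-label phase, as at lower doses.
- Extend the first package by one day, from 21 to 16 + 6 = 22 days.

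The cost is a short amendment, plus one extra titration day and one phone call per participant who reaches 2.0 mg/day, so at most 40 calls with 40 enrolled. No extra participants or visits are needed. Intolerance that first appears later in the open-label phase can stay with the investigator under Sections 7.1 and 12, which need no change.

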#### Scales to assess adverse events related to the study medication

UKU side effect rating scale: The UKU side effect rating scale is a short and easy-to-use instrument that captures the core dimensions of side effects in patients using psychotropic medications. The UKU side effect rating scale is widely used in both research and in clinical settings (57), and is delivered by interviewing and observing the patients and their caregivers. Herein, we will adopt the UKU side effect rating scale specifically adjusted to adults with IDD, which consists of 35 items out of the original 48 items. This revised checklist seems more feasible to observe items that are concrete and objective than items based on the patients' subjective experiences (58). Approximately 20 minutes to complete.

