#### Other measures

1. Demographic questionnaire
2. Current and Concomitant medications (including type, dose, and duration of treatment)\*
3. Height
4. Weight
5. Vital signs (blood pressure, heart rate, and temperature)
6. Drug diary to evaluate compliance

---

\*The high dose of benzodiazepine (more than the benzodiazepine equivalent to lorazepam 2 mg daily) and other cannabinoids, which are still used 4 weeks before the start of the use of the study drug (titration phase), are not permitted. Other concurrent medications and non-medication treatments (including behavioural therapy, psychological therapy, occupational therapy, support group etc.) are permitted before and during the trial.

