## **8. SAMPLE SIZE AND DATA ANALYSIS**

To test the Hypotheses 1 and 2, we aim to enroll 40 patients to enter the dose titration phase, consistent with common sample sizes for Phase I trials (63).

We assume the attrition rate of 25% from the dose titration phase to entering the open-label phase. To test behavioural changes at the group level (Exploratory Objective), the sample size of the remaining participants (N=30) could be sufficient to detect differences with effect size Cohen's d as low as of 0.53, and at power = 0.8 and two-sided  $\alpha$ -level = 0.05 (G\*Power 3.1), which is similar to that detected in the study investigating the effects of nabilone on agitation associated with dementia (27).

Paired-t test will be used to investigate the pre- vs. post-treatment behavioural and brain changes. Exploratory analyses will be performed to determine predictors of response including baseline individual features, using logistic regression. Safety profiles will be described in the percentage of each adverse effects. For MRI measures, non-parametric tests will be used to explore the brain changes with nabilone treatment, assuming that only few participants can finish MRI scans eventually.

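### The UKU side-effect scale has no rating before the first dose, so symptoms that predate nabilone can enter its adverse-event percentages

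*Protocol*

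**What the plan says.** **Schedule.** In Protocol Table 1 the UKU row is marked for titration, open-label, V 1 and V-F. The screening and V 0 cells are empty. The prose agrees: neither the V 0 list in Section 3.1 nor the screening and baseline lists in Section 3.2 name the UKU. Its first full use at a visit is V 1, where adverse events are assessed "using the UKU side effect rating scale, examined by the researcher or investigator, to systemically investigate the physical AEs of nabilone".

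**Use between visits.** On the titration calls the study team looks for physical or mental changes thought to be adverse events, with the UKU as its guide. On the weekly open-label calls, "If there are any changes suspected to be associated with AEs, the UKU side effect rating scale will be assessed during the telephone check-up".

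**Other safety measures.** These do have a pre-dose value. The V 0 list includes "Measuring baseline vital signs and weight to monitor any AEs of nabilone", and the NIH Toolbox is also given at V 0.

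**The instrument and background drugs.** Section 3.4 says the UKU "captures the core dimensions of side effects in patients using psychotropic medications", in a version of 35 items adapted for adults with IDD. Apart from the restrictions listed, concurrent medications "are permitted before and during the trial" (Section 3.4, Other measures, footnote).

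**Analysis.** Section 8 states: "Safety profiles will be described in the percentage of each adverse effects". Hypothesis 2 expects these rates to be lower than published rates for antipsychotics in IDD.

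**The concern.** In a single-arm, open-label trial, the participant's own state before dosing is the only internal comparator. The main adverse-event instrument is the one repeated safety measure without it.

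The gap matters in this population. Section 1.2 puts psychotropic prescribing at up to 70% of adults with IDD. The exclusion criteria bar a psychotropic change in the 4 weeks before study drug, not stable use, and they allow benzodiazepines and hypnotics up to stated limits. The UKU was built to pick up side effects of psychotropic drugs in general. A positive item on nabilone may therefore reflect an older drug or a long-standing condition. Drowsiness, the reaction listed most often for nabilone in Section 9.3 (66.0%), is a symptom that could already be present.

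The safety profile is the primary objective and is meant to inform later randomised trials. If old and new symptoms are mixed, the percentages do not describe what nabilone adds. A rate inflated by residual antipsychotic effects would also be set against literature rates for antipsychotics.

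**Working it through.** **The plan's own figure.** The protocol gives no calculation for the safety outcome. Its only computed figure is the detectable effect for the exploratory paired t-test: 40 × (1 − 0.25) = 30 participants and d = 0.53 at 80% power. It reproduces (power 0.801 at d = 0.53, two-sided 0.05) and has no bearing on this point.

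**Inputs.** N = 40 enter titration (Section 8). The UKU takes about 20 minutes (Section 3.4). Two quantities are not in the documents and are assumed: b, the share with a given item before dosing, and i, the share of the remainder who newly develop it on nabilone.

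**Formulas, for one item, with no filtering of pre-existing symptoms.**
- Recorded on treatment: b + (1 − b) × i
- New onset among all participants: (1 − b) × i
- Excess: the difference between the two, which is exactly b
- Pre-existing share of those counted: b / [b + (1 − b) × i]

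**Results with i = 20%.**

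| b | Recorded | New onset, all participants | Recorded / new, of 40 | Pre-existing share |
|---|---|---|---|---|
| 10% | 0.10 + 0.90 × 0.20 = 28% | 18% | 11.2 / 7.2 | 36% |
| 20% | 0.20 + 0.80 × 0.20 = 36% | 16% | 14.4 / 6.4 | 56% |
| 40% | 0.40 + 0.60 × 0.20 = 52% | 12% | 20.8 / 4.8 | 77% |

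**Sensitivity to i.** With i = 10%, the same three values of b give 19%, 28% and 46% recorded, against 9%, 8% and 6% new onset.

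**Effect of filtering.** If start dates or causality judgement remove a fraction f of the pre-existing cases, the excess falls from b to (1 − f) × b. The protocol gives no basis for a value of f, so the table is an upper bound for each b.

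**The case against.** The strongest reply is that not every positive UKU item becomes a reported adverse event. Section 12 makes the AE log the record, with a start date, a resolution date and a judgement of relationship to the drug. The titration calls ask about changes. The UKU is completed by interviewing and observing both participant and caregiver, who may know that a symptom is old. The V-F rating, two weeks after full discontinuation, gives a reading off nabilone, and an item still present then speaks against a nabilone effect.

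This stands in part. It rules out the stronger reading a reader might infer, that pre-existing symptoms will all be counted or can never be recognised. But start dates would rest on recall, the causality judgement is unblinded and has no earlier UKU rating to refer to, and Section 8 does not limit the percentages to new or related events. V-F comes after exposure and cannot show whether an item present both before and during treatment became worse.

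Two other readings also fail:
- **That events in the stable phase go unasked.** Section 12 has AEs assessed at every telephone follow-up. Only the full UKU depends on a suspected change.
- **That the gap flatters nabilone.** Counting old symptoms raises its rates and works against Hypothesis 2. Judgement without a baseline could, however, also dismiss a real worsening as pre-existing.

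It is fair to add that a treatment-emergent definition is commonly left to the SAP, which is not at hand, so its absence from the protocol is not the finding. The missing rating is different: no SAP can recover data that were never collected.

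**Conclusion.** The point holds as a gap in data collection. Table 1 and the visit lists agree that no UKU is taken before dosing, so symptoms that predate nabilone can enter the primary safety percentages, and the existing safeguards reduce this only in part.

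The size is not known from the documents. In the worst case the excess for an item equals its prevalence before dosing: 10, 20 or 40 percentage points in the illustration. That assumes i = 20% and no filtering. The right comparator is new onset among all participants (18%, 16% or 12%), not a constant 20%, which is the rate only among those free of the symptom at the start.

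This should be fixed but does not undermine the trial. Safety is described rather than formally tested, the likely bias runs against the sponsor's hypothesis, and other safety measures have baselines. It needs doing before the first dose because the rating cannot be obtained afterwards.

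**What to change.** Add the UKU at V 0, before the first dose: mark the V 0 cell in Table 1 and add the scale to the V 0 list in Section 3.1 and the baseline list in Section 3.2. In Section 8, base the reported UKU percentages on items that are new, or worse in severity, compared with V 0.

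The cost is one interview of about 20 minutes per participant at an existing visit. Table 1 already allows the UKU in person or virtually. For 40 participants this is 40 × 20 = 800 minutes, about 13 hours. The sample size does not change. The weekly open-label calls need no change for this purpose.
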